## Assignment of interventions: allocation

### Sequence generation {16a}

A computer-generated randomization schedule will be used to allocate the 192 participants into one control group and two experimental groups in a 1:1:1 ratio. The randomization will be performed using simple randomization without stratification. The sequence will be generated by an independent statistician to ensure allocation concealment and minimize potential bias in the assignment process.

### Concealment mechanism {16b}

A sealed, opaque, and consecutive envelope will be prepared for each participant. Each envelope will contain the group assignment determined by the randomization sequence. The envelopes will be opened sequentially only after a participant is deemed eligible and has provided informed consent, ensuring that the allocation remains concealed until the point of assignment. This approach prevents foreknowledge of group assignments and minimizes selection bias.

### Implementation {16c}

The randomization sequence was generated by the statistical team of the clinical research center of the eye hospital of Wenzhou Medical University. Specialized ophthalmologists in the outpatient clinic will recruit potential participants and conduct baseline assessments. Once participants confirm their enrollment, researchers will assign the corresponding envelope based on the order of participant enrollment. The envelope will then be opened by an independent research assistant, who will use the random number inside the envelope to determine the group assignment.

## Assignment of interventions: blinding

### Who will be blinded {17a}

Due to the nature of the intervention, blinding of participants and intervention providers is not feasible. However, to minimize potential bias, the examination equipment is relatively objective and blinding will be implemented for outcome assessors, data collectors, and data analysts.

Outcome assessors: Independent examiners conducting refraction and AL measurements will be blinded to the participants’ group assignments. They will not be involved in intervention delivery or participant interactions beyond data collection.

Data collectors: Personnel responsible for recording and entering study data will be blinded to group allocation to prevent unconscious bias in data handling.

Data analysts: Statistical analysts will receive a coded dataset without group identifiers, ensuring that data analysis remains objective.

Blinding procedures will be strictly maintained throughout the study to enhance the reliability and validity of the findings.

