### Trial design {8}

This study will be a randomized, superiority-controlled trial with a parallel-group design. One hundred ninety-two pre-myopic children will be randomly divided into three groups of 64 subjects in a 1:1:1 ratio. The three groups are no use of DIST, DIST alone (RIO-Max 2.0), and DIST optimized by combining the optical defocusing technique (RIO-Ultra 2.0). The complete study flowchart is shown in the figure (Fig. 1). The protocol and all study procedures are approved by the Medical Ethics Committee of the Affiliated Eye Hospital of Wenzhou Medical University (2024–016-K-015–05) and conducted following the ethical standards of the Declaration of Helsinki. The protocol has been registered with the Chinese Clinical Trial Registry (ChiCTR2400082078) and uses the SPIRIT reporting guidelines [25]. Subjects are required to sign an ethical informed consent form before participating in the experiment.

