### Strategies to improve adherence to interventions {11c}

To enhance participant adherence, each participant will be assigned a dedicated research assistant who will maintain regular contact with the participant’s family through a dedicated WeChat group. The research assistants will offer support by addressing any questions, troubleshooting equipment issues, and sending reminders to ensure timely completion of the intervention and follow-up activities. For experimental groups using DIST, the research team will monitor the device’s usage through backend records once a week to verify adherence to the required usage duration. If any irregular usage patterns are detected, the research assistants will promptly inform the participant’s family and provide personalized guidance to ensure consistent adherence.

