## Statistical methods

### Statistical methods for primary and secondary outcomes {20a}

Analysis of primary outcomeIn this participant-based study, the primary outcome is the proportion of myopia onset. This outcome is measured as a binary (nominal) variable. Participants are classified as either having experienced the onset of myopia (Yes) or not (No), based on whether their cycloplegic spherical equivalent refractive error reaches or exceeds − 0.50 D in either eye at the 1-year follow-up. This is a single endpoint measure, assessed once at the end of the 1-year follow-up period. It provides a proportion of participants who experience the onset of myopia. To test the effectiveness of DIST on the primary outcomes, logistic regression including trend analysis will be used, which can both examine the overall relationship and detect potential trends related to different treatments. In addition, covariates such as baseline spherical equivalent refractive error, age, gender, and study group (Intervention vs. Control) will be included to ensure a parsimonious logistic regression model while controlling for factors known to influence myopia onset and progression.The primary analysis will be conducted on the ITT population, which is defined as all randomized participants with at least one post-baseline measurement. For all analyses, the underlying model assumptions will be rigorously evaluated. For instance, when applying logistic regression to assess the binary primary outcome, we will verify the linearity of the logit for continuous covariates using methods such as the Box–Tidwell test, assess multicollinearity via variance inflation factors (VIF), and examine residuals and influence statistics (e.g., Cook’s distance) to identify any influential outliers. Missing data will be addressed using multiple imputations by chained equations under the assumption of data missing at random (MAR), with sensitivity analyses planned to assess the impact of outliers, nonadherence, and loss to follow-up.Analysis of secondary outcomesThe secondary outcomes are intended to capture aspects of the intervention effect that are not fully reflected by the primary outcome. For example, even if the primary outcome (myopia onset) does not show a statistically significant difference, significant changes in spherical equivalent or axial length may still be observed, thereby indicating a potential benefit of the intervention in slowing myopia progression.For the three secondary outcomes: (1) the proportion of fast progressors over 1 year, (2) changes in spherical equivalent progression, and (3) changes in AL (mm) at each follow-up point, the following statistical procedures will be employed:Proportion of fast progressors (binary outcome)This endpoint will be analyzed using logistic regression. The model will estimate the odds of being classified as a fast progressor over 1 year, comparing the intervention group to the control group. Covariates to be included in the model are baseline spherical equivalent refractive error (continuous), age (continuous), and gender (categorical), as these factors have been shown in prior research to influence myopia progression. The study group (intervention vs. control) will be the primary factor of interest. These covariates are selected based on their theoretical relevance and empirical support, ensuring a parsimonious model that controls for potential confounding without overfitting.Changes in spherical equivalent progression (continuous outcome)The change in spherical equivalent progression over time will be analyzed using a repeated measures mixed-effects model. This model will account for within-subject correlations across multiple follow-up points and will include fixed effects for the treatment group, time (as a categorical or continuous variable depending on the observed pattern), and the interaction between treatment and time. Baseline spherical equivalent refractive error, age, and gender will be included as covariates to adjust for initial differences and known predictors of refractive change. The rationale for these covariates is their established association with myopia progression, ensuring that the model is both explanatory and parsimonious. Model selection procedures, such as stepwise backward elimination based on the Akaike Information Criterion (AIC) or likelihood ratio tests, will be applied to refine the final model.Changes in AL (mm)Similar to the spherical equivalent endpoint, changes in axial length (measured in mm) at each follow-up will be analyzed using a repeated measures mixed-effects model or an analysis of covariance (ANCOVA) for longitudinal data. The model will include fixed effects for treatment, time, and their interaction. Covariates will include baseline axial length, baseline spherical equivalent, age, and gender. These factors are chosen because they are known to influence ocular growth and, consequently, axial elongation. As with the other endpoints, a parsimonious model will be achieved by using stepwise selection methods or likelihood ratio tests to retain only covariates that contribute significantly to explaining the variation in axial length change.The results of these analyses will be presented as adjusted odds ratios with 95% confidence intervals for the binary outcome and as least-squares means (LSMEANS) with standard errors for the continuous outcomes. In addition, p-values will be reported to assess the statistical significance of the observed differences between intervention groups.Analysis of exploratory outcomesTime-to-myopia onset analysisFor comparing the time to myopia onset (time-to-event outcome) among 3 treatment groups, we all create a number-at-risk table and use the Kaplan–Meier method to estimate survival curves, followed by the log-rank test to assess differences statistically.Myopia onset associationsA logistic regression model will be built with myopia onset as the dependent variable and near-work duration, device usage duration, and confounding factors as independent variables. The near-work duration was derived from the near-work log cards and questionnaires, with the daily averages taken for analysis. Odds ratio (OR) and its 95% confidence interval will be estimated to determine associations while controlling for confounding.Dose–response relationship analysisWe will group near work and device usage durations (e.g., by quartiles). Use the Cochrance–Armitage trend test to analyze if there’s a dose–response relationship. Curve fitting (such as polynomial regression) can also be used to further explore the non-linear relationship between them.Choroidal thickness changesFor exploring changes in choroidal thickness during different follow-up periods among three groups, repeated measures analysis of variance (ANOVA) will be used. If significant effects are found, post hoc tests (like Bonferroni or Tukey’s) will determine specific differences.

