### Stratification and definition

Participants will be stratified into subgroups based on predetermined thresholds for both device usage and near work duration. For the purposes of this study, we will operationally define high-intensity near work behavior as a daily at-home near work duration of 2 h or more, while near work behavior lasting less than 2 h per day will be classified as low-intensity.

All participants will be included in the analysis. Adherence, defined as the ratio of actual device usage duration to planned usage duration, is calculated as both daily (daily adherence (%) = actual daily training duration/planned daily training duration × 100%) and overall (overall adherence (%) = ∑ (actual daily training duration)/∑ (planned daily training duration) × 100%). Subsequently, according to the adherence categories established by the Pediatric Eye Disease Investigator Group (PEDIG) [27, 28] (“excellent” (76%–100%), “good” (51%–75%), “fair” (26%–50%), and “poor” (0%–25%)), participants with an average daily device usage of 30 min or more will be classified as having high adherence, while those with less than 30 min per day will be classified as low adherence. These thresholds may be refined based on the statistical distribution of the relevant data at the end of the study.

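### Analyst blinding by a coded dataset cannot hold for the control arm once device-usage or adherence data are in the analysis file

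*Protocol article*

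**What the plan says.** Section {17a} accepts that participants and those delivering the intervention cannot be blinded, and relies on blinding outcome assessors, data collectors and data analysts instead. For analysts: "Statistical analysts will receive a coded dataset without group identifiers, ensuring that data analysis remains objective". For data collectors: "Personnel responsible for recording and entering study data will be blinded to group allocation to prevent unconscious bias in data handling". The section closes by saying that blinding will be strictly upheld for the duration of the study.

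On the arms, Trial design {8} states: "The three groups are no use of DIST, DIST alone (RIO-Max 2.0), and DIST optimized by combining" with optical defocus. On usage records, Strategies to improve adherence {11c} says: "For experimental groups using DIST, the research team will monitor the device" through weekly backend logs. On the analyses, section {20a} plans a logistic model for myopia onset with "near-work duration, device usage duration, and confounding factors as independent variables".

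**The concern.** Removing the group label hides the arm only if no other variable in the file reveals it. Device usage is such a variable: children in the control arm have no device, no backend log and no planned usage. An analyst working with a file that contains it can tell which code is control.

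This matters because several analysis choices remain open. If they are settled by someone who can see which arm is control, they can be settled with the treatment effect in view. Participants and providers are already unblinded, so analyst masking is one of the few protections left, and the protocol presents it as sufficient for objectivity.

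**Working it through.** No formula applies beyond a head count. The check follows the usage variable through the protocol article.

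1. **Who has the variable.** Usage is logged for the device arms only ({8}, {11c}). Section {16a} will "allocate the 192 participants into one control group and two experimental groups in a 1:1:1 ratio", so the expected control arm is 192 / 3 = 64 children and the device arms together 192 − 64 = 128. Because randomization is simple, 64 is an expected figure, not an exact one.

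2. **Who needs the variable.**
   - {20a}: the onset-association model and the dose-response trend test use device usage duration.
   - {20b}: subgroup and interaction models use it for axial length and myopia incidence.
   - Stratification and definition: adherence is actual over planned device use. The section puts all participants in the analysis. A control child has no planned usage, so the ratio has no denominator.
   - {20c}, PP analysis: membership depends on having used the device as instructed.

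3. **What an analyst sees.** In a file with these fields, device children have positive usage histories, while controls are blank, zero or undefined. Matching that pattern to the arm codes identifies the control code. It does not separate DIST alone from the combined arm, since both have usage records.

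4. **Is release staged?** Nothing in the article says that usage data are held back until other results are final, or that different analysts handle them.

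5. **Data entry and roles.** Data management {19} sends everything collected into the electronic database by double entry. Staff who enter usage data would therefore see who has a device, although {17a} says: "Personnel responsible for recording and entering study data will be blinded to group allocation". Section {5d} also has one research team sharing delivery of the intervention, outcome evaluation, data management and analysis. That needs reconciling with {17a}.

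6. **What is still open at analysis.**
   - Missing data: multiple imputation under {20a}, last observation carried forward for the ITT analysis under {20c}. This touches the primary result.
   - Spherical equivalent: time as categorical or continuous, according to the pattern observed.
   - Axial length: mixed model or ANCOVA.
   - Continuous secondary outcomes: stepwise covariate selection.
   - Subgroup cut-offs: "These thresholds may be refined based on the statistical distribution of the relevant data at the end of the study".

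**The case against.** The best defence is that the article never says analysts receive a single merged file before the primary analysis. Backend logs, a questionnaire spreadsheet and the electronic database are described separately, and the primary model needs only baseline refraction, age, gender and group. The timing of a merge is ordinarily left to an analysis plan or data-management plan that is not shown here. This stands in part: one cannot say that the control arm is certain to be unmasked when the file is opened. It does not remove the contradiction, because {17a} claims blinding throughout and treats a coded dataset as enough, while the protocol's own usage analyses defeat that.

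The primary outcome is also a fixed cut-off on cycloplegic refraction, measured by examiners separately said to be blinded, with named covariates. That stands, and it limits the harm to analysis choices.

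Two stronger readings are tempting and not supported. A reader might infer that the case report forms carry usage or adherence. The listed contents in {18a}, and the additions in {11d} and {22}, do not include either, and the stated source is backend records. A reader might also infer that adverse-event or near-work log-card fields reveal the arm. The symptoms asked about in {22} can occur with ordinary near work, and the Discussion does not restrict the log card to the device arms.

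Finally, coded arms alone do not fully mask even the primary model, since {20a} specifies intervention versus control and a trend across treatments. That is correct, and the fix has to deal with it.

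**Conclusion.** The claim of analyst blinding in {17a} is too broad. It fails for the control arm, about 64 of 192 children, in any analysis file that includes device usage or adherence. It can hold for DIST alone versus the combined arm on this variable. For data-entry staff the point is an inference from {19} and {5d}, not a stated fact.

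The conclusion assumes that no staged release is specified in a document not shown. If one is, the wording of {17a} still needs correcting. A reader might go further and infer biased outcome measurement. The document does not show that, and it gives no basis for sizing any bias. The risk lies in the analysis choices that remain open, which makes this a change worth making rather than a threat to the trial's validity.

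**What to change.** 1. Keep backend usage and adherence in a separate file, handled apart from the outcome data.
2. Release coded arms, baseline covariates, refraction and axial length first. On these, settle missing-data handling and model choices, then lock the primary and secondary results.
3. Have the control code and the arm order for the trend test applied by someone outside the analysis team, or only after lock.
4. Then merge usage for the per-protocol, adherence and dose-response analyses.
5. Limit the claim in {17a} to analyses that do not use device-usage data, state that the usage-based analyses are not blinded, and reconcile {17a} with the shared team roles in {5d}.
6. Fix the usage thresholds in Stratification and definition beforehand. Staging does not protect them, because they can be refined only with usage data in hand.

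The cost is revised wording, a split export and a short delay before the usage analyses, with no extra participants or visits. It is probably still timely: recruitment ended in September 2025, so 12-month visits run to about September 2026, after this version's date of March 2026.

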### Procedure for unblinding if needed {17b}

N/A.

## Data collection and management

### Plans for assessment and collection of outcomes {18a}

At baseline and during each follow-up, researchers will provide paper-based questionnaires for guardians to complete, and the results will be entered into a spreadsheet for analysis. All other clinical assessments will be performed by experienced clinicians using relevant measuring instruments (as specified in item 12). Measurements will be repeated to ensure the reliability and validity of the data collection. Meanwhile, patients’ general information, medical history, baseline and follow-up results, adverse event reports, and trial summaries will be recorded in the CRFs by researchers on time. All researchers and clinicians will undergo training on participant recruitment, assessment, intervention, and data backup before participating in the study.

Cycloplegic autorefraction will be performed using the Topcon KR800 autorefractor unit following the cycloplegia regimen of 1% cyclopentolate (Cyclogyl, AlconConvreur). The procedure involves administering two drops of 1% cyclopentolate separated by a 5-min interval, followed by a 30-min resting period after the final instillation. Complete cycloplegia is confirmed by the absence of fluctuation in retinoscopy findings under cycloplegic conditions in children or by performing autorefraction combined with careful subjective refraction. Spherical equivalent is calculated as spherical power plus half of the cylinder power. Cycloplegic measurements will be performed at baseline, the 6-month follow-up, and the 12-month follow-up to assess the primary outcome.

Ocular AL will be measured on a Zeiss IOL Master 700 (Carl Zeiss Meditec Inc.) using noncontact partial coherence interferometry. Perform six measurements of total AL, anterior chamber length, and corneal curvatures. At least three measurements are identical or almost identical. The ChT will be measured using Wevis OCT (Wevis Imaging Technology Co., Ltd.) in the Angio 6 × 6 512 R4 mode. Each image covers a 6 × 6 mm area centered on the fovea. Researchers will use the OCT’s built-in software to automatically center the image and segment the choroidal thickness. Choroidal thickness is defined as the perpendicular distance between the outer choroid-sclera margin and the retinal pigment epithelium–Bruch’s membrane complex. The subfields analyzed are delineated using the standard ETDRS 9-segment grid, including the central zone (0–1 mm), the four quadrants of the inner ring (1–3 mm), and the four quadrants of the outer ring (3–6 mm). After measurement, all images will be checked for signal quality and segmentation accuracy. If the signal quality is too low or segmentation errors are present, the measurement will be repeated.

Questionnaires are used to assess children’s subjective visual experience during near work. The assessment focuses on visual comfort (e.g., fatigue, eye pain, blurred vision) and behavioral manifestations such as lack of concentration or reading difficulties during near tasks. Additionally, evaluating the time spent on outdoor activities and near work provides insights into myopia risk associated with lifestyle habits.

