#### Exploratory outcomes

*Time from randomization to occurrence of myopia (time-to-event outcome)*: The time from randomization to the occurrence of myopia will be measured as a time-to-event outcome. This endpoint will provide further insights into how quickly DIST delays the onset of myopia compared to the control group.*The association between near-work duration at home and myopia onset*: The duration of near-work activities (e.g., reading, using electronic devices) at home will be correlated with the onset of myopia to investigate environmental factors influencing myopia development. This data will help clarify the role of lifestyle factors in conjunction with DIST intervention.*The association between device usage duration and myopia onset*: The duration of DIST device usage will be correlated with the onset of myopia to explore potential dose–response relationships. This will determine whether longer usage of DIST is associated with a greater effect on myopia prevention, while controlling for other near work behaviors.*Changes in choroidal thickness (ChT) (µm) at 6 and 12 months follow-ups*: Changes in choroidal thickness will be monitored as an exploratory endpoint to assess the potential underlying physiological mechanisms of DIST technology in myopia prevention. Changes in choroidal thickness or blood flow as biomarkers of myopia progression are of significant importance in myopia prevention and control research.*Side effects and adverse events*: The occurrence of side effects and adverse events will be closely monitored throughout the study to ensure the safety of the DIST intervention. This will include any ocular or systemic issues reported by participants, and the severity of these events will be recorded.

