#### Type I error rate (alpha), power level (e.g., 80% power)

Type I error rate (α): 0.025/2 = 0.0125

Power (1-β): 80%

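### Exploratory choroidal thickness is analysed by repeated-measures ANOVA without its baseline as covariate and with no summary across nine subfields; one baseline-adjusted model would be better

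*Protocol article*

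**What the plan says.** Under Exploratory outcomes the protocol lists a single ChT outcome, "Changes in choroidal thickness (ChT) (µm) at 6 and 12 months follow-ups", and gives its purpose: "Changes in choroidal thickness will be monitored as an exploratory endpoint to assess the potential underlying physiological mechanisms of DIST technology in myopia prevention".

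Under Plans for assessment and collection of outcomes {18a}, the measurement paragraph says "The subfields analyzed are delineated using the standard ETDRS 9-segment grid". It counts one central zone, four inner quadrants and four outer quadrants. It does not name a lead zone or an average.

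Under Statistical methods for primary and secondary outcomes {20a}, the ChT entry says that "repeated measures analysis of variance (ANOVA) will be used. If significant effects are found, post hoc tests" follow, with Bonferroni and Tukey as examples. It names no covariate and does not say how the nine subfields enter the analysis. In the same section the SE model lists baseline SE, age and gender as covariates, and the AL model lists baseline AL, baseline SE, age and gender. Table 1 schedules OCT at enrolment, 6 months and 12 months, so baseline ChT is available.

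**The concern.** There are two separate issues.

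The first is precision. ChT is the only continuous outcome in section {20a} whose planned model leaves out its own baseline value, although that value is collected. Subtracting the baseline removes most of a chance imbalance between arms but not all of it, because change is still correlated with the starting value. Covariate adjustment removes the rest and narrows the intervals.

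The second is that one listed outcome becomes nine analysed readings, and the protocol does not say which reading or summary answers the question. The Bonferroni or Tukey step follows a significant ANOVA and separates the arms. Nothing says that it also covers the subfields. If the readings were tested one by one, a single nominally significant quadrant could be put forward as a sign of a choroidal mechanism.

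The stakes are limited to the mechanistic reading of the trial.

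**Working it through.** The protocol gives no alpha, sample size or error rate for ChT, so there is no stated figure to reproduce.

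**Inputs from the protocol**
- Nine subfields (section {18a}).
- Three arms of 64 (Trial design {8}). With the anticipated 20% dropout, 64 × 0.8 = 51.2, so about 51 per arm.
- ChT change at 6 and 12 months, with a baseline OCT (Exploratory outcomes; Table 1).

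**Inputs assumed, because the protocol does not give them**
- Baseline to follow-up correlation r of ChT: 0.80 to 0.95.
- Correlation ρ between subfields, equal for all pairs: 0.5 to 0.9.
- Per-test alpha of 0.05. The only stated alpha is "Type I error rate (α): 0.025/2 = 0.0125", and it belongs to the myopia-incidence sample size.

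**Step 1: cost of omitting the baseline.** Take one follow-up visit, with equal variance σ² at both time points.
- Variance of the change: 2σ²(1 − r).
- Residual variance after adjusting for baseline: σ²(1 − r²).
- Ratio: (1 + r)/2.
- At r = 0.95 the ratio is 1.95/2 = 0.975, a saving of 2.5%. At r = 0.80 it is 1.80/2 = 0.90, a saving of 10%.

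Under randomisation the unadjusted change comparison keeps its type I error. The loss is in precision only.

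**Step 2: false arm effects if each subfield were tested separately.** With nine independent tests at 0.05 the chance of at least one is 1 − 0.95⁹ = 37.0%. For correlated subfields, nine three-arm F tests with no true effect were simulated (40,000 trials per setting):

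| ρ | 51 per arm | 64 per arm |
|---|---|---|
| 0.5 | 27.5% | 27.6% |
| 0.6 | 24.3% | 24.4% |
| 0.7 | 21.2% | 20.7% |
| 0.8 | 17.3% | 17.0% |
| 0.9 | 12.9% | 13.0% |

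A smaller simulation (6,000 trials) gave about 10% at ρ = 0.95 and about 7% at ρ = 0.99. That simulation used three visits per child and an assumed within-child correlation of 0.8. If either the arm or the arm-by-visit test counted as an effect, it gave about 24% at ρ = 0.9 and 49% at ρ = 0.5. At a per-test alpha of 0.0125 the chance of at least one false arm effect is about 4% to 9% for ρ of 0.9 to 0.5.

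**Step 3: what one summary does.** A single arm test at 0.05, on the grid average or as one overall arm test with subfield as a factor, has a 5% chance of a false effect. With equal subfield variances, the variance of the nine-subfield mean relative to one subfield is (1 + 8ρ)/9. At ρ = 0.5 this is 5/9 = 0.56, and at ρ = 0.9 it is 8.2/9 = 0.91. An effect common to all subfields is therefore estimated more precisely on the average.

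**The case against.** The strongest reply is that the protocol nowhere says nine separate ANOVAs will be run. One model with subfield as a within-eye factor, or a grid average, fits its words just as well. ChT is expressly exploratory, and the Discussion calls for further work on mechanisms. The choice of a lead subfield and multiplicity across subfields are commonly left to the SAP, which is not shown. All of this stands. It means that the lack of a named lead subfield is largely missing detail, and that the Step 2 figures are conditional.

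A reader might infer that the plan itself carries a 13% to 27% false-positive rate, partly because baseline ChT is left out. The documents do not support that. Separate testing, the 0.05 level and the correlations are all assumed, and the missing covariate adds nothing to the figure.

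A reader might also think that letting a pure visit effect open the post hoc tests inflates error among the arm pairs. It does not, because Bonferroni and Tukey control those pairs without any preceding gate.

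The contrast with the SE and AL models is softened too: the protocol allows model selection in both, so their covariates are not fully fixed.

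The objection does not reach the stated method itself. The article goes as far as naming the model, the post hoc step and the subfields for ChT. The model it names makes no use of a baseline that is collected and that the neighbouring models use.

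**Conclusion.** The point holds as a modest improvement to an exploratory analysis. The planned ChT analysis is valid but less precise than it could be, by about 2.5% to 10% of variance if r lies between 0.95 and 0.80 with equal variances over time. That loss does not touch the type I error. The multiplicity risk is real only if subfields are tested one at a time. It would then be about 13% to 27% at a per-test 0.05 and ρ of 0.9 to 0.5, smaller at higher correlation or a stricter level. These figures describe one permitted reading of the text and are not a property of the plan. Primary and secondary inferences are unaffected.

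**What to change.** In the ChT entry of section {20a}, replace the repeated-measures ANOVA with one model of ChT change at 6 and 12 months, adjusted for baseline ChT, age, gender and baseline SE. Use either the average over the grid as the outcome, or all nine subfields with subfield as a within-eye factor. In both cases make one overall arm (or arm-by-visit) test the basis for inference. Report the individual subfields descriptively, with intervals and no significance claims, and add a matching sentence to the measurement paragraph in section {18a}.

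The cost is wording only, since the baseline OCT is already scheduled. The one downside is that an effect confined to a single subfield would be described and not tested. Recruitment is stated to have finished in September 2025, so 12-month visits can run to about September 2026. The change is best made before those data are analysed.
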